### Questionnaire-based measures

Participants will also complete a battery of questionnaires by verbally conveying their responses to a researcher who will type the participant’s response directly into the REDCap database. Paper questionnaires will be available for participants who wish to complete the questionnaires independently and as back-up in case of IT issues or participant processing difficulties. In these instances, the researcher will enter data onto the dedicated forms on the REDCap database following the assessment.

Questionnaires include the following: (a) the Depression, Anxiety and Stress Scales (DASS-42) [27], a 42-item measure of the severity/frequency of negative affective symptoms that are rated on a 4-point scale ranging from ‘never’ to ‘almost always’; (b) the EuroQual of life scale (EQ-5D-5L) [28], which measures five dimensions of health status including mobility, self-care, usual activities, pain/discomfort and anxiety/depression across five levels ranging from ‘no problems” to ‘unable/extreme problems’, alongside a visual analogue scale to provide a self-report of individual health status; (c) the ICECAP measure for adults (ICECAP-A) [29], which assesses five capabilities relevant to wellbeing including stability, attachment, autonomy, achievement and enjoyment; (d) the Positive emotion, Engagement, Relationships, Meaning, and Accomplishment (PERMA) profiler [30], a 23-item measure to assess flourishing across 5 domains (PERMA) as well as health, negative emotion, loneliness and overall happiness on a 11-point scale ranging from not at all/never to completely/always; and (e) an adapted version of the Client Service Receipt Inventory (CSRI) — Mental Health Version [31], which captures individual health service usage data.

### Psychophysiology

A Polar H10 heart rate sensor will be attached to a chest strap, placed around the chest wall and positioned below the pectoral muscles. The participant will then be placed in a seated position and left alone for 10 min, while heart rate variability data are collected. The Polar H10 device will be connected to the Elite HRV application [32], which will be installed on an iPad and connected to a secure NHS network, and the collected data will be exported as a plain text file to this network. The data file contains only millisecond timings between heartbeats and the unique study identification number. No personal information that can identify a participant will be included in this data file. Prior to data collection, participants will be asked some lifestyle questions regarding physical activity, time of last meal, alcohol intake, smoking status, sleep, height and weight. Prior work has demonstrated that the data collected from the Polar H10 devices are highly correlated with the hospital-grade electrocardiogram (*r* = 0.997) [33].

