### The intervention

Over the last few years, we have developed an 8-week-positive psychotherapy intervention [14, 15, 24] involving one session per week over the 8-week period. Our treatment manual has been reiterated several times based on our previous clinical experience of running this group, user feedback and developments in wellbeing science. The present study will aid in further refining our intervention and materials including a clinician manual and participant workbook. Table 1 provides a summary of session-by-session content across the 8-week intervention.

**Table 1 Tab1:** Session-by-session summary of 8-week-positive psychotherapy course for people living with acquired brain injury^a^

Session no. and name	Summary of session content
Session 1: Living with difficult emotions	• Difficult emotions are understandable following brain injury • A series of exercises encourage participants to accept such emotions • Participants learn coping skills, e.g., a ‘defusion exercise’ • Also includes focus on mindful breathing exercises and self-compassion • Difficult emotions motivate reflection and/or need for helpful changes • ‘Snakes and ladders’ adaptation helps to make content memorable
Session 2: Identifying and using character strengths	• Discussion of the nature of character strengths • Participants discuss results from a character strengths questionnaire • Discussion of how participants might use their strengths • Positive impacts of character strengths use are emphasised • Positive self-statements are created on which a positive introduction is built • ‘Snakes and ladders’ framework used to reinforce relevant concepts
Session 3: Building positive emotion	• Positive emotions have psychological and health benefits • They also help to cope with stress and adversity • Participants complete a ‘Getting to Know Your Lemon’ mindfulness exercise • Discussion of psychological flow, learned optimism and existential gratitude • Activities include mindful eating exercise and the ‘three good things’ activity • Participants complete meaning and values clarification exercise • Snakes and ladders’ framework is again used to reinforce relevant concepts

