Session 4: Connection between body and mind	• Participants learn about the mechanisms of the mind–body connection • Focus on positive health behaviours, e.g., healthy diet, sleep, exercise • Regulatory role of the vagus nerve, indexed by heart rate variability (HRV) • Other techniques, e.g., singing, meditation, cold showers improve HRV • Participants explore acute impacts of different activities on own HRV • Highlights need for self-care, contextualised by healthy mind–body connection
Session 5: Connection to others and the natural environment	• Focuses on connecting to others and nature, and links to health and wellbeing • Science behind these connections, and how to improve wellbeing • Responding to good news and events, e.g., active-constructive responding • Variety of gratitude exercises, loving kindness meditation, volunteering • Nature-based activities good for wellbeing (e.g., gardening) • Also good for the environment (e.g., pro-environmental behaviours) • Participants complete a ‘photo-journalist exercise’
Session 6: Meaning and purpose	• Meaning and purpose give us a sense of direction and motivation in life • May be enhanced and facilitated by focus on the self, collective and planet • Discussion of photos representing areas of meaning for participants • Areas of meaning linked to personal values as per exercise in Session 3 • Behaviour-intention gaps constrain the translation of values into action • Reflection on how those gaps might be overcome
Session 7: Translating values into action	• Recap on participant's strengths, values and important areas of meaning • Explore extent to which participants are living a values-based life • Participants identify and share areas where they are acting out their values • Areas where they could better connect with their values are explored • Participants set goals that support them to reconnect with some of their values • Thoughts and feelings serve as barriers / facilitators to acting out values • Return to the metaphor of ‘snakes and ladders’

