**Fig. 1 Fig1:**
[figure not shown]
Flowchart of enrolment, interventions and assessments

**Table 2 Tab2:** Schedule of enrolment, interventions and assessments for participants (P) and their mentors (M)

Activity	Timepoints				
	**Eligibility checks**	**Baseline assessments**	**Psychotherapy sessions (1–8)**^**a**^	**Immediate follow-up**	**3-month follow-up**
Consent	P, M				
Eligibility checks	P, M				
• RBANS	P, M				
• SASNOS	P, M				
Data collection					
• HRV		P, M		P, M	P, M
• DASS-42		P, M		P, M	P, M
• PERMA Profiler		P, M		P, M	P, M
• EQ-5D-5L		P, M		P, M	P, M
• ICECAP-A		P, M		P, M	P, M
• Demographics		P, M			
• CSRI		P, M		P, M	P, M
Randomisation		P			
Intervention			P^a^, M		
Focus group				P^a^, M^b^	

*RBANS* refers to the Repeatable Battery for Assessment of Neuropsychological Status, *SASNOS* refers to St. Andrews-Swansea Neurobehavioral Outcome Scale, *HRV* refers to heart rate variability, *DASS-42* refers to the Depression, Anxiety and Stress Scales, PERMA-Profiler refers to the Positive emotion, Engagement, Relationships, Meaning, and Accomplishment Profiler, *EQ-5D-5L* refers to the EuroQual of life scale; *ICECAP-A* refers to the ICEpop CAPability measure for Adults, *CSRI* refers to an adapted version of the Client Service Receipt Inventory

^a^Intervention group only. TAU participants do not attend meetings or the focus group

^b^Intervention group participants and mentors attend separate focus groups

The wellbeing and care of participants will be prioritised throughout the study, providing support during data collection sessions, which involves the administration of measures of distress, well-being and quality of life. Any significant difficulties will be fed back to the wider clinical team to ensure that appropriate support is provided.

Any modifications to these procedures will be submitted to the Wales Research Ethics Committee for approval after which an updated version of the protocol will be made available at the ISRCTN Trial Registry (10.1186/ISRCTN12690685).

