### Quantitative data

This feasibility trial will explore the most appropriate primary outcome for a fully powered RCT. Data analysis, following intention-to-treat principles, will focus on descriptive statistics and feasibility outcomes, consistent with the primary aims and objectives of the trial. Summaries, including completeness, for outcome measures and important demographic covariates will be reported by group. No missing data will be imputed. While clinical effectiveness will not be definitively assessed at this stage, we will explore hypotheses that measures of depression, anxiety and stress (as operationalised by the DASS) will diminish, and measures of PERMA and HRV will improve, using a split-plot ANOVA with group (intervention vs control) as a between-subjects factor across time (pre vs two follow-up assessments), a within-subject factor. All assessments will be summarised using two-sided tests and 95% confidence intervals where appropriate. Estimates of treatment effect size and intraclass correlations will be used to inform sample size considerations for a full-scale RCT.

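### The HRV recording, as described, does not separate a lasting change in resting HRV from PP participants using a taught technique while being recorded

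*Protocol article*

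**What the plan says.** **Intervention content (Protocol article, The intervention, Table 1).** Session 1 teaches breathing skills: "Also includes focus on mindful breathing exercises and self-compassion". Session 4 presents HRV as an index of vagal regulation and tells participants how to raise it: "Other techniques, e.g., singing, meditation, cold showers improve HRV". They then try this on themselves: "Participants explore acute impacts of different activities on own HRV". Session 8 reviews the techniques and provides resources for practising them.

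**Who receives it.** The PP group and the mentors. A footnote to Table 2 states: "TAU participants do not attend meetings or the focus group".

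**The recording (Psychophysiology).** "The participant will then be placed in a seated position and left alone for 10 min, while heart rate variability data are collected". Lifestyle questions asked beforehand cover physical activity, last meal, alcohol, smoking, sleep, height and weight. On the export: "The data file contains only millisecond timings between heartbeats and the unique study identification number". Table 2 schedules HRV at baseline, immediate follow-up and 3-month follow-up.

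**Use of the result (Quantitative data).** The hypotheses to be explored include that "measures of PERMA and HRV will improve". They are examined by a split-plot ANOVA with group as the between-subjects factor. Treatment effect sizes are to inform sample size considerations for the full RCT.

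**The concern.** One arm is taught that a particular physiological signal matters, that certain techniques raise it, and that its acute response to activities can be seen. That arm is later recorded on the same signal, seated and alone for 10 minutes, which is a natural setting for meditation or a breathing exercise. Nothing described in the article registers whether a technique was used.

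A higher HRV in PP at follow-up could therefore reflect a lasting change in resting physiology, a technique used during those 10 minutes, or both. Randomisation and the baseline recording do not remove the ambiguity, because the teaching comes after both and is tied to one arm.

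The stake is interpretation. Among the outcomes repeated at follow-up in Table 2, HRV is the only one that is not a questionnaire, so a rise may be given particular weight as an early sign of benefit. An HRV effect size inflated in this way could also enter the planning of the RCT.

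**Working it through.** The protocol states no HRV effect size or HRV-based sample size, so there is no figure to reproduce. The check is mainly a comparison of stated conditions, followed by an illustration under assumptions.

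**1. Conditions by arm and visit**

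| | Baseline | Both follow-ups |
|---|---|---|
| PP: trial teaching on HRV and how to raise it | not yet given | given (Session 4) |
| TAU: trial teaching on HRV | none | none |
| Possible mindfulness within TAU care | not stated | listed as an option under Treatment as usual |
| Recording | seated, alone, 10 min | same |
| Question on technique use | none listed | none listed |

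The recording conditions are the same in both arms. What participants know about the signal differs between arms at follow-up only. The group-by-time contrast is therefore exposed to the difference.

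**2. Expected direction**

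Session 4 itself says that the techniques improve HRV. If they are used during the recording and work as taught, PP values rise. Use by TAU participants who have learned mindfulness would raise TAU values too.

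**3. Size, under assumptions**

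Let q be the share of PP participants using a technique during the recording, r the share in TAU, and a the acute shift in SD units. With no lasting effect at all:

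bias = (q − r) × a

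None of q, r or a is in the documents. Taking r = 0:

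- q = 0.3, a = 0.5: 0.3 × 0.5 = 0.15 SD
- q = 0.5, a = 0.5: 0.5 × 0.5 = 0.25 SD
- q = 0.5, a = 1.0: 0.5 × 1.0 = 0.50 SD

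Any r above zero reduces these values.

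**4. What such a bias could do**

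The Randomisation section aims for 10 per site per arm, so 3 × 10 = 30 per arm. For a simple two-group comparison at one follow-up, two-sided alpha 0.05, SD 1 and no dropout:

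- Chance of a significant difference favouring PP = Φ(bias / √(2/30) − 1.96), with √(2/30) = 0.258.
- Per-arm size of an RCT planned on that value at 80% power = 2 × (1.96 + 0.84)² / bias².

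| Bias (SD) | Chance of significance favouring PP | RCT size per arm if taken as the effect |
|---|---|---|
| 0 | 2.5% | – |
| 0.15 | 8% | 698 |
| 0.25 | 16% | 252 |
| 0.50 | 49% | 63 |

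This is simpler than the planned split-plot ANOVA and ignores the baseline recording, group delivery and dropout. It shows the order of magnitude only.

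**The case against.** Several points on the other side stand.

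- **An instruction may exist.** A reader might infer that participants are recorded with no instruction at all. The article does not say so. It condenses a fuller protocol, and wording spoken to the participant is the kind of detail left to an operating procedure. What remains is that the participant is alone, so compliance with any instruction would go unobserved, and no later check is described.
- **The two explanations are not inseparable.** A reader might infer that technique use can never be told apart from resting change. The exported beat-to-beat intervals allow breathing frequency to be estimated, which would flag at least slow paced breathing. The supportable claim is that the described procedure does not make the separation.
- **The direction is expected, not fixed.** Treatment as usual may include mindfulness and acceptance and commitment therapy, so TAU participants may have related skills. Only the HRV-specific teaching is confined to the PP sessions.
- **Use during the recording is not shown.** Nothing in the documents indicates that any participant would do this. Of the techniques named in Session 4, cold showers are impossible in that setting and singing is unlikely. Meditation, and the mindful breathing from Session 1, are feasible.
- **HRV is exploratory.** The primary endpoints are the Table 3 criteria, none of which uses HRV, and the protocol says that effectiveness will not be definitively assessed. That HRV might become the RCT's primary outcome is an inference: the plan says that it will explore the choice, without naming HRV.
- **Using a taught skill is arguably a treatment effect.** That is a legitimate reading, but a different one from a lasting resting change. The Background presents the psychophysiological measures as measures of wellbeing, so a report needs to be able to say which meaning its HRV difference carries.

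**Conclusion.** The concern holds as a plausible bias that has not been ruled out. It arises where stated intervention content meets a stated measurement set-up, and so goes beyond missing detail. As described, the exploratory HRV contrast mixes any lasting change in resting HRV with technique use during the recording, and the expected direction favours PP. The same applies to an HRV effect size carried into RCT planning.

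The documents do not give its size. The range of 0.15 to 0.5 SD rests wholly on the assumed shares and shifts, and on no technique use in TAU. The true value could be negligible. The conclusion leaves the feasibility endpoints, and the decision rules built on them, untouched. The point is worth acting on because the remedy is cheap and mostly uses data already exported.

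**What to change.** For the present trial:

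1. After each remaining recording, in both arms, ask one yes/no question on whether a breathing, meditation or other technique was used.
2. Estimate breathing frequency from the exported beat-to-beat intervals.
3. Report the HRV contrast with and without recordings flagged by either route.
4. Word any HRV difference as not necessarily a change in resting HRV, including where it informs RCT sample size.

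Use an identical script (sit quietly, breathe normally, do no exercises) for participants not yet measured at baseline, and in the future RCT. It should not be introduced between visits for participants already measured, since that would change recording conditions between baseline and follow-up.

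The protocol expected the last visit by the end of October 2023. If recordings are complete, steps 2 to 4 remain available, with flags from breathing frequency alone.

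The cost is one CRF item and one sensitivity summary with a few recordings excluded. Breathing frequency identifies technique use only in part, and the yes/no answer is self-reported, so the check narrows the ambiguity without removing it.

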### Qualitative measures

Focus groups will be conducted with those participants allocated to the intervention group to facilitate a better understanding of study feasibility, clarify the components that participants like and dislike and help to determine what does and does not work. Questions regarding acceptability and participants’ experiences of the trial procedures and of the wellbeing intervention itself will be addressed through focus groups. A semi-structured interview schedule will cover topics including recruitment and data collection procedures, as well as experiences of participating in the group (see Supplementary information for a copy of this schedule). This will be implemented flexibly to facilitate group discussion and collection of rich and detailed data regarding participant experience, especially with regard to improvements needed for a future full-scale trial. The focus groups will be conducted by a female clinical trial coordinator who has a postgraduate background in psychology, facilitating a comfortable and confidential environment. Clinical staff members will be located nearby for governance purposes. Participants will be reminded about the purpose of the focus group, and that their data will be anonymized and potentially used for evaluation purposes. The interviewer will encourage group discussion by actively engaging participants in meaningful conversations and understanding the basis for differences in perspectives.

To ensure accuracy, the audio files of the focus groups will be transcribed using an orthographic approach. This transcription method includes incorporating verbal cues like ‘ah’, ‘um’ and other similar expressions. Additionally, grammatical correctness will be maintained to indicate pauses, the end of statements and exclamations. The focus groups will be transcribed verbatim, except for the exclusion of participant names, staff names and locations to safeguard anonymity.

### Analysis

As a feasibility trial, our primary endpoints are based on the criteria outlined in Table 3. We will also report descriptive statistics concerning adverse events, categorized by factors such as seriousness and severity, within each arm of the study. Adverse events will be continuously assessed as they are reported to determine their relevance to the trial design and the intervention at regular intervals.

**Table 3 Tab3:** Criteria, measurement and the pass/fail system to determine study feasibility

Criteria	Measurement and justification	Fail	Pass
Recruitment across sites	Successful enrolment and recruitment rates will be monitored. Information will include number of participants recruited, number of participants declining and reasons for declining, and number of participants retained. Establishing a 50% recruitment rate threshold acknowledges the challenges inherent in recruiting individuals with ABI while also ensuring that the resources allocated to the study including time, funding and personnel are maximised. Recruitment rate will be determined as the % of target N recruited. The percentage of patients invited who agree to take part in the intervention will also be calculated	Issues at 1 + sites	All three sites recruit eligible patients
Recruitment rate (%)		< 50%	≥ 50%
Randomisation process	Randomisation process failures are defined as randomising an ineligible patient, a breakdown of the randomisation process and failure to adhere to the randomisation allocation. Maintaining a low threshold for randomisation process failures helps to ensure reliability and validity of trial outcomes	2 + issues with randomising	< 2 issues randomising participants
Intervention compliance (%) — clinicians	Adherence to the treatment manual as assessed by review of a content checklist, completed by the group facilitator at the end of every session at each of the three sites. Setting a threshold of 80% ensures a high standard of intervention fidelity across sites while still accounting for minor deviations that may occur due to contextual factors or facilitator styles	< 80%	≥ 80%
Intervention adherence (%) — participants	Attendance at a minimum of six sessions will be used to measure adherence. Full or partial completion of the two pieces of mandatory homework allocated to participants during session 1 and session 5 will also be documented. Setting the threshold at 75% ensures that participants are engaging in at least six of eight sessions of the intervention while also mindful of potential challenges participants may face such as scheduling conflicts and unexpected circumstances	< 75%	≥ 75%
Data collection	Success would be indicated if completion rates for post-intervention assessment and follow-up data collection reach a satisfactory threshold, taking into account practical considerations including participant compliance and capacity, versus representativeness and generalisability. Missing data will be reported	< 70%	≥ 70%
Attrition rates	Attrition will be calculated as the percentage of participants dropping out of the study relative to the numbers recruited. Reasons for withdrawal and loss to follow-up will be reported. Setting an attrition threshold at 40% acknowledges the potential challenges of participant retention in longitudinal studies	≥ 40%	< 40%

In the event that any of the feasibility criterion fail to meet the established targets for progression (Table 3), a comprehensive assessment will be undertaken that explores the reasons for the failure and determines the appropriate course of action. Based on that assessment as well as more general considerations relating to the detailed acceptance checklist [19], the research team will consider available options to address the feasibility challenges with the aim of optimising recruitment strategies and trial design. Ultimately, the decision to progress to a full-scale randomized controlled trial (RCT) will be based on a careful evaluation of the feasibility challenges in relation to the team’s capacity to run a future trial with confidence and achieve its objectives. The aim will be to strike a balance between addressing the identified challenges and ensuring the feasibility and success of the full-scale RCT. This approach will enhance the team’s ability to gather robust data, meet scientific standards and ultimately contribute valuable insights to the field of study.

These feasibility data will be complemented by inspection of additional quantitative, qualitative, psychophysiological and health economic data, as outlined in further detail below.

